### Data analysis

Effect analyses will be performed both on 'intention to treat' and per protocol principles. Differences between intervention and usual care patients at 6 months on the outcome measures (risk adjusted interRAI LTCF based Quality indicators, EuroQoL, functional health and disability) will be compared between the intervention and control group by both univariate and multivariate techniques. We will use the multivariate technique to adjust for possible differences in baseline scores and background variables between the intervention and control groups. Dropout and loss to follow up will be described. Potential effect-modification will be explored.

Especially, possible differential effects of disease management will be explored across residents with complex and simple health problems.

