### Procedure

All residents from the usual care homes as well as from the intervention homes receive an invitation letter and an informed consent form two weeks before the start of the study. If the resident is not able to understand the information and/or to sign the informed consent papers a close family member will be invited to participate and provide proxy information on the outcomes.

All eligible persons who sign an informed consent are going to be visited by an interviewer of the VU medical centre for an interview on their health and resource use. Table 1 provides an over-view of the measurements.

**Table 1 T1:** Overview of outcomes and measurements in the study

Variable	Instrument	Baseline	6 months
*Primary outcome*			
a. Quality of Care	RAI-LTCF criteria	X	X
b. Quality Adjusted Life Years	Euroqol & thermometer	X	X
c. Functional health	COOP-WONCA & SF12	X	X
*Secondary outcome*			
d. Patient care satisfaction	Brief Quote on elderly Homes	X	X
e. Disability ADL-IADL	Groningen Activity Restriction Scale	X	X
f. Mood disorders	PRIME-MD	X	X
g. Hospital days	Checklist resource utilization Hospital records	X	X
h. Time to nursing home placement	Registration elderly home HIS		X
i. Time to mortality	Registration elderly home HIS		X
Economic outcomes			
Direct costs	Patient/family Interview Registration pharmacy Registration medical records		X
*Process outcomes*			
Adherence professionals to disease management protocol	Checklist		X
Adherence of patients to specific disease management recommendations	Checklist		X
Potential Effect Modifiers			
-Sociodemographics	Patient Interview	X	
-Health status (morbidity, medication)	Patient Interview Patient records	X	X
-House & personnel characteristics	Staff Interview	X	

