#### Primary outcomes are

1. Quality of care as measured with the risk adjusted criteria [27],

2. Quality Adjusted Life Years using health utilities is measured with the Euroqol [28,29],

3. Functional health is measured by COOP-WONCA charts [30,31] (Nelson 1983, Van Weel 1995) and Short Form 12 item version [32].

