#### Cost effectiveness analysis

For the cost-effectiveness analysis the difference in total costs between the intervention and usual care group are compared with the difference over 6 months in improvement of functional health and disability. In addition, a cost utility analysis will be done to assess the incremental costs per Quality Adjusted Life Years (QALY). QALY's are calculated by multiplying the utility based on EuroQol scores [29] with the amount of time a patient spent in this particular health state. Transitions between health states are linearly interpolated.

Uncertainty around the cost-effectiveness and cost-utility ratios is calculated using the bias-corrected percentile method (5000 replications) and presented in a cost-effectiveness plan [39]. The bootstrapped cost and effect pairs will also be used to calculate cost-effectiveness acceptability curves [40].

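### QALYs are declared a primary outcome, but the effect analysis compares the EuroQol at 6 months, a quantity that leaves out residents who die and, unadjusted, treats baseline differently

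*Protocol article*

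**What the plan says.** Four places in the protocol article bear on this outcome.

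- **Primary outcomes list:** "Quality Adjusted Life Years using health utilities is measured with the Euroqol". It does not state the period. Six months follows from the follow-up given under Design.
- **Table 1 (Procedure):** the QALY row is a primary outcome with instrument "Euroqol & thermometer", taken at baseline and 6 months only.
- **Cost effectiveness analysis:** "QALY's are calculated by multiplying the utility based on EuroQol scores" by the time spent in each health state, and "Transitions between health states are linearly interpolated". Its stated use is economic: "a cost utility analysis will be done to assess the incremental costs per Quality Adjusted Life Years (QALY").
- **Data analysis:** "Differences between intervention and usual care patients at 6 months on the outcome measures (risk adjusted interRAI LTCF based Quality indicators, EuroQoL, functional health and" (one further item, disability, closes the list). On method, the section says that these "will be compared between the intervention and control group by both univariate and multivariate techniques". The multivariate analysis is there to "adjust for possible differences in baseline scores and background variables between the intervention and control groups". QALYs are not named in this section.

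No section says that EuroQol at 6 months stands for the accumulated QALY, or how residents who die enter the comparison.

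**The concern.** The declared primary outcome accumulates over follow-up, whereas the compared variable is a state at the end of it. The article fixes both, so the mismatch is not a detail left to an unseen analysis plan.

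Two things are at stake. First, a resident who dies contributes a shortened QALY but has no 6-month EuroQol score, so the comparison as written drops residents whom the declared outcome counts. Mortality is a listed secondary outcome, so deaths are expected. Second, two EuroQol-based results can come out of one trial, one from the effect analysis and one from the cost-utility analysis, and a reader cannot tell which decides the primary outcome. The Background says designs are published so that intended and final outcomes can be compared, and this ambiguity works against that.

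**Working it through.** **Inputs from the article.** EuroQol at 0 and 6 months (Table 1); follow-up 0.5 year (Design); linear interpolation (Cost effectiveness analysis); unadjusted and adjusted comparisons (Data analysis). The article gives no QALY difference to reproduce, and no utility level, SD or mortality rate.

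**Assumptions.** Baseline utility u0 with mean 0.60 and SD 0.25; 6-month utility u6 = u0 − 0.03 + effect + noise with SD 0.20; death times uniform over follow-up (mean 0.25 year); utility held at u0 until death and 0 afterwards.

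**Step 1. QALY of a survivor.** Q = 0.5 × (u0 + u6)/2 = 0.25(u0 + u6).

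**Step 2. Adjusted comparison, survivors.** Regress Q on arm and u0. The term 0.25·u0 is absorbed by the baseline covariate, so the arm coefficient is 0.25 times the coefficient for u6, and its standard error shrinks by the same factor. A simulated data set confirms this: 0.0621 for u6, 0.0155 for Q, t = 3.28 for both. The choice of variable makes no difference here.

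**Step 3. Unadjusted comparison, survivors.** Let D0 and D6 be the arm differences at baseline and 6 months. The QALY contrast is 0.25(D0 + D6); the effect analysis tests D6.

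- D0 = −0.04, D6 = +0.03: 0.25 × (−0.01) = −0.0025.
- D0 = −0.02, D6 = +0.03: 0.25 × 0.01 = +0.0025.

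The signs differ when D0 and D6 have opposite signs and |D0| > |D6|. With SD 0.25, 250 residents per arm in homes of 50, correlation 0.6 and a true effect of 0.03, they differ in about 15% of simulated trials for an ICC from 0 to 0.10.

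**Step 4. Deaths.** The mean QALY of an arm with mortality m is (1 − m) × 0.25 × (0.60 + 0.57 + effect) + m × 0.60 × 0.25.

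| Utility gain | Deaths, intervention v control | QALY difference | 6-month EuroQol difference, survivors |
|---|---|---|---|
| 0 | 5% v 10% | 0.05 × (0.2925 − 0.15) = +0.0071 | 0 |
| 0.05 | 10% v 5% | 0.2895 − 0.2854 = +0.0041 | +0.05 |
| 0.03 | 12% v 7% | 0.2820 − 0.2825 = −0.0005 | +0.03 |

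When utilities are kept within −0.3 to 1, simulation gives about +0.007, +0.003 and −0.001 for the QALY, and about 0, +0.045 and +0.027 for the EuroQol. With equal mortality of 10%, the two agree to within about 13% after rescaling by 0.25.

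**Step 5. Sensitivity to the pre-death path.** Take survivors' 6-month means of 0.63 v 0.60 and deaths of 10% v 5%. Holding utility at 0.60 until death gives 0.29175 − 0.2925 = −0.0008. If those who die start at 0.40 and fall linearly to 0 at 3 months, with each arm's overall baseline kept at 0.60, the result is −0.0032.

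**Step 6. Size against sampling error.** The survivor QALY SD is about 0.25 × √(4 × 0.0625 + 0.04) = 0.135. With 250 per arm the standard error is 0.135 × √(2/250) = 0.012 before clustering. The 0.0071 of the first table row is about 0.6 of a standard error; −0.001 is under a tenth of one.

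**The case against.** The best defence is that EuroQol is shorthand. The Abstract lists the outcome as QALYs with Euroqol in brackets, Table 1 pairs the two, the QALY is the only EuroQol-based outcome declared, and an accumulated QALY is also known at 6 months. This reading is possible. It is not the natural one, because the list compares values at 6 months alongside functional health and disability scores. If shorthand was meant, one clause settles it.

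A reader might infer that the trial never analyses its declared primary outcome. The documents do not support that: the incremental cost per QALY requires the QALY difference between groups, and the cost and effect pairs are bootstrapped. What is missing is the QALY in the effect analysis.

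A reader might also infer that the two results will often contradict each other. Step 2 rules that out for baseline-adjusted survivors. The reversals that arise through deaths need an intervention that improves utility while raising mortality, and they are tiny. Residents expected to die within six months are excluded, which lowers mortality without removing it.

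Nor do the documents say that QALYs were chosen in order to capture survival. Time to mortality is a separate secondary outcome and dropout is to be described, so deaths are not ignored. They are, however, absent from the comparison for this primary outcome.

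**Conclusion.** The concern holds in a limited form. The declared outcome (QALY) and the compared variable (EuroQol at 6 months) are different quantities, and the article does not reconcile them. They give the same test among survivors with baseline adjustment. They part through residents who die and in the unadjusted comparison, where the QALY contrast is 0.25(D0 + D6) rather than D6.

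The clearest consequence is that a survival difference does not show in the planned comparison: about 0.007 QALY against about 0 on the EuroQol, with assumed deaths of 5% v 10% and no utility effect. Sign reversals through deaths are possible but small, between −0.0005 and −0.0032 in the cases worked here, and they move with the assumed mortality and pre-death utility. The numerical differences are small against sampling error. The case for change rests on having one defined primary outcome that counts every resident.

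**What to change.** In the Data analysis section, replace EuroQoL in the list of compared outcomes by: *QALYs over 6 months, derived as in the cost-utility analysis, with utility 0 from the date of death, and adjusted for baseline EuroQol utility*. Keep the 6-month EuroQol score as a supportive outcome.

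The baseline adjustment is an essential part of the change. A QALY contains baseline utility, so an unadjusted QALY contrast would carry any imbalance between ten homes into the effect.

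The cost is wording: the QALY derivation is already planned and days until death are already recorded. The small downside is an assumption about the utility path between baseline and death. State it and vary it in a sensitivity analysis, for example utility held at baseline until death against a linear fall to 0.

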## Methods

### Design

A cluster randomized controlled clinical trial is carried out among five intervention homes and five usual care homes for the elderly in the north-west of the Netherlands that comprise over five hundred residents. There is a follow up of six months (Figure 1). The ethical committee of the VU medical center approved the study.

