### Randomization

The randomization is carried out on home matched by percentage of psycho geriatric (i.e. cognitive impaired) residents. The care services and type of disability in homes with a high percentage of psycho geriatric patients are likely to differ depending on how many residents need psycho geriatric care. So, the homes were first ranked on percentage of psycho geriatric patients. The two homes with the highest percentage of psycho geriatric patients were than matched, and so on.

Next, we checked the risk of imbalance in numbers following Pocock's recommendations [23]. If the difference in number of intervention and control residents would be >15% (75 or more) the randomization should be repeated until the imbalance was 15% or less.

Homes were all ordered on the percentage psycho-geriatric patients and numbered from rank one to rank 10. In this way matched homes are ranked after each other, one having an even and the other an uneven number. Randomization was carried out using Pocock's first column in his random numbers table [23]. If the table's first number is even, the even number of first matched home is assigned the intervention. If the next table number is uneven, the uneven number of the next matched couple is assigned the intervention. And so on until all matched couples are assigned.

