### Sample size calculation

Sample size calculations are based on the expected effects of the intervention on the main outcome measures concerning quality of care and functional health. In the following sample size calculations we used an alpha of 0.05, power of 80% and inflation of 10% because of anticipated intra-cluster correlation in the homes for the elderly. Regarding health related quality of life, Cohen's D effect size ranged from 0.5 to 3.8 in our meta-analysis [22]. To detect a fair benefit, i.e. effect size = 0.5, a minimum of 64 persons is needed in each group [35]. For functional health and disability we anticipate on a comparable effect-size and consequently identical sample size. Furthermore if we assume a dropout rate of 15% during the 6 months follow-up we need to include at least 100/85 × 64 × 110% = 82 persons in each group.

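### Homes are randomised in five matched pairs, but the stated effect analysis compares residents between arms and names no method that accounts for home or pair

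*Protocol article*

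**What the plan says.** All places are in the protocol article.

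- **Design:** the trial has "five intervention homes and five usual care homes for the elderly in the north-west of the Netherlands that comprise over five hundred residents".
- **Randomization:** "The randomization is carried out on home matched by percentage of psycho geriatric (i.e. cognitive impaired) residents". Homes are ranked on that percentage, neighbours in the ranking form pairs, and one home of each pair receives the intervention.
- **Sample size calculation:** the inputs are "alpha of 0.05, power of 80% and inflation of 10% because of anticipated intra-cluster correlation in the homes for the elderly". No ICC is given.
- **Data analysis:** six-month differences between patients of the two arms "will be compared between the intervention and control group by both univariate and multivariate techniques". The multivariate technique is there to adjust for baseline scores and background variables. The section does not mention home, pair, clustering, a multilevel model or robust variances.
- **Discussion:** the authors name it as a possible weakness that cultural differences between homes will not be balanced across the two arms.

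**The concern.** The design and the sample size treat the home as a source of correlation; the effect analysis does not. Residents of one home share staff, physicians and routines, so their outcomes tend to be alike. A test that counts each resident as independent takes its precision from the number of residents, when the allocation gives only five homes against five. Any positive between-home variance that matching and covariates do not remove then makes the standard error too small.

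This affects the p-values and confidence intervals of the outcomes that the section lists: quality indicators, EuroQol, functional health and disability. A chance difference between two sets of five homes could pass for an effect of the disease management model.

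**Working it through.** **1. The plan's own sample size.** Inputs: "effect size = 0.5, a minimum of 64 persons is needed in each group", two-sided 5% (sidedness is not stated, but two-sided reproduces the figure) and 80% power. The t test gives 64 per group (power 80.2%). The final step is "100/85 × 64 × 110% = 82 persons in each group"; exactly, 100/85 × 64 × 1.10 = 82.8. The figure reproduces (83 if rounded up, which is immaterial). The clustering allowance is therefore a design effect (DE) of 1.10.

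**2. What that allowance implies.** With DE = 1 + (m − 1) × ICC and m residents per home:
- m = 50 (500 residents in 10 homes): ICC = 0.10/49 = 0.002.
- m = 16.4 (82 per group in 5 homes): ICC = 0.10/15.4 = 0.0065.

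**3. Type I error if residents are treated as independent.** The standard error is too small by a factor √DE, so the true level of a nominal 5% test is 2 × [1 − Φ(1.96/√DE)].

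At DE = 1.10: 1.96/1.049 = 1.869, giving **6.2%**.

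The ICCs below are assumptions. The value m = 42.5 is 50 per home less the protocol's 15% dropout.

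| Residents per home | ICC 0.01 | ICC 0.02 | ICC 0.05 |
|---|---|---|---|
| 16.4 | DE 1.15: 6.8% | DE 1.31: 8.7% | DE 1.77: 14.1% |
| 42.5 | DE 1.42: 9.9% | DE 1.83: 14.7% | DE 3.08: 26.4% |
| 50 | DE 1.49: 10.8% | DE 1.98: 16.4% | DE 3.45: 29.1% |

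**4. Effect of matching.** The table assumes no gain from matching. In a simulation of five matched pairs (40,000 runs per scenario) in which matching removes half of the between-home variance, the resident-level test rejects in 7.9%, 10.7% and 19.0% of runs at 50 per home, and in 5.8%, 6.7% and 9.4% at 16 per home, for ICC 0.01, 0.02 and 0.05.

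**5. Analyses by home.** In the same simulations a paired t test on home means (4 df, critical value 2.78) rejects in 4.8–5.3% of runs in every scenario. An unpaired t test on home means (8 df) holds 5.0–5.1% when matching has no effect. It becomes conservative (2.4–4.7%) when pairs share half of the variance and the matching is ignored.

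**6. Power of analyses by home.** For d = 0.5 with no gain from matching; 14 completers per home follows from 82 × 0.85/5 = 13.9:

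| Completers per home | ICC | Paired, 4 df | Unpaired, 8 df |
|---|---|---|---|
| 14 | 0.01 | 56% | 69% |
| 14 | 0.05 | 42% | 53% |
| 42 | 0.01 | 89% | 96% |
| 42 | 0.05 | 60% | 73% |

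**The case against.** The strongest reply is that this is a condensed article. It does not name the multivariate model or say that residents will be treated as independent, and a random home effect could stand in a fuller plan. That is fair, and it rules out stating as fact that the trial will be analysed as if individuals had been randomised. It does not dispose of the point. The section does state the unit (patients), the contrast (arm against arm), a univariate comparison that as worded has no place for home, and a purpose for the multivariate technique that concerns covariates and not dependence. The same article goes into detail elsewhere, down to the number of bootstrap replications.

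Three stronger readings are tempting, and the document does not support them:

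- *The type I error is well above 5%.* A reader might infer this from the larger entries in the first table. They rest on an assumed ICC, on 42–50 residents per home and on no gain from matching or covariates. The figure of over five hundred is what the homes house, not what is enrolled: consent is required and terminally ill residents are excluded. The protocol's own allowance gives about 6%.
- *The matching variable is left out of the model.* The background variables are not listed, and Table 1 collects characteristics of the house and its personnel at baseline, so this is unproven. A home-level covariate alone would not correct the standard errors, however.
- *Five pairs can never reach the 5% level.* An exact pair-wise permutation test cannot go below 2/2⁵ = 0.0625, but that floor does not apply to a paired t test on home means or to a model with pair effects.

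The authors also disclose that homes differ in culture. Disclosure does not widen a confidence interval.

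**Conclusion.** The point stands in conditional form and should be settled before analysis. The protocol randomises homes and anticipates intra-cluster correlation, but its stated effect analysis contains nothing that reflects homes or pairs. Followed as written, it is anti-conservative for any between-home variance left after matching and adjustment. The direction is secure; the size is not, because the article gives no ICC. The defensible range runs from about 6% at the protocol's own design effect, through 7–14% at the planned minimum, to 10–29% with 42–50 residents per home. The last two ranges assume an ICC of 0.01 to 0.05, and both fall if matching works.

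**What to change.** Replace the resident-level comparison in Data analysis, including the univariate test, with one analysis that respects randomisation by home. Either of these is valid:

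- a mixed model with a random intercept for home; arm, the resident's baseline score and the matching variable (or pair) as fixed effects; and Kenward-Roger or Satterthwaite degrees of freedom; or
- a two-stage analysis of baseline-adjusted home means on a t distribution, either paired (4 df) or unpaired with the home's percentage of psychogeriatric residents as a covariate (10 homes − 3 parameters = 7 df).

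Choose one before outcome data are seen and state the ICC that is assumed.

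No new data are needed. The cost is wider confidence intervals and less power. If only 82 per group are recruited, a paired analysis at ICC 0.01 has about 56% power for d = 0.5, short of the planned 80%; with about 42 completers per home it has about 89%. The change is therefore affordable if most residents of the ten homes take part, and the sample size section should say so.

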### Process evaluation

The process evaluation involves assessing the extent to which the intervention program is performed according to protocols, the nature of the recommendations made to the participants of the MM, compliance with these recommendations, physicians and therapists judgments about the intervention program and recommendations. Data on these topics are collected using structured registration forms during the intervention. Finally, semi-structured interviews will be held with the participating nurses, primary care physicians, and nursing home physicians at the end of the intervention period in order to record their experiences and opinions on the new disease management model.

### Economic evaluation

Cost data are collected by resident interview at base line, and at 6 months from a societal perspective and supplemented with resource use as registered within the home for the elderly. In case residents are cognitively impaired or not able anymore to be interviewed, proxies will be sought, preferably close family members. Only direct healthcare costs will be considered, because all patients have retired. Included cost categories are costs of consultations with the general practitioner, the nursing home physician and medical specialists, hospitalizations and admissions to the medical department of the nursing home and use of medication and medical aid. Medication data are retrieved from the centralized pharmacy files in the research region. Care consumption will be valued according to guidelines for economic evaluation in health care in the Netherlands [36,37].

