### Chronic disorders and homes for the elderly in the Netherlands

In our aging population the number of persons with a chronic disease is expected to increase from 1994–2015 with 25–60% [18]. In the Netherlands there are about 110.000 residents in homes for the elderly [4]. Professional care is needed for 71% of the residents such as assistance with activities of daily living or mobility, nursing care (medication, wound care etc) and domestic help. Twelve percent of persons of 75 years and older live in a home for the elderly and 4% in a nursing home [19]

The quality of care in these homes is frequently discussed in national and international newspapers. The care organizations responsible for the quality of care given in homes for the elderly often do not have the tools to measure and improve quality of care. Scientific studies of quality of care for the elderly are rare.

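### The listed cost categories price nursing-home admissions but not days or daily care in the home for the elderly, so the cost difference is biased if home days or in-home care differ between arms

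*Protocol article*

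**What the plan says.** The Economic evaluation section sets the frame: "Cost data are collected by resident interview at base line, and at 6 months from a societal perspective". It then narrows it: "Only direct healthcare costs will be considered, because all patients have retired". The content of the cost total follows as a list: "Included cost categories are costs of consultations with the general practitioner, the nursing home physician and medical specialists, hospitalizations and admissions to the medical department", continuing "of the nursing home and use of medication and medical aid", where it ends. Neither the stay in the home for the elderly nor the nursing, personal or domestic care given there is named.

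Two other sentences in the section bear on the point. The interview data are "supplemented with resource use as registered within the home for the elderly", and "Care consumption will be valued according to guidelines for economic evaluation in health care in the Netherlands". Neither says that home days or daily care enter the total.

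Under Cost effectiveness analysis, "the difference in total costs between the intervention and usual care group are compared" with the effects on functional health and disability. A cost-utility analysis per QALY and acceptability curves follow.

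Nursing-home placement and mortality are both secondary outcomes with dates. The Abstract says that consultation is directed at the frailest residents, those at risk of nursing-home admission.

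**The concern.** Every participant lives in a home for the elderly, and the model under test works through the care given there: assessment by nursing staff, individual care plans, and triggers such as rehabilitation potential in daily activities (Intervention(s), Table 2). The background section on chronic disorders says of Dutch homes in general: "Professional care is needed for 71% of the residents such as assistance with activities of daily living or mobility, nursing care". That is a statement of need, not of hours used by trial residents, but it shows that in-home care is not a marginal item.

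The list prices one side of a transfer and not the other. When a resident leaves for a listed nursing-home bed, the new days are charged and the home days that end are not credited. A resident who survives longer in the home gains QALYs, because these are utility multiplied by time, while the extra days carry no stay or daily-care cost. A change in care intensity inside the home would also go unrecorded in the total if the list is followed literally. Any such error passes into the cost difference, both ratios and the acceptability curves.

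**Working it through.** The article states no unit price, placement rate or cost result, so there is no figure of its own to reproduce. The check is an accounting identity with labelled assumptions.

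**Notation.** n = price of a nursing-home day; h = price of a day in the home for the elderly; dNH and dH = intervention minus control difference in mean nursing-home days and mean home days per resident.

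**Identity.** Full cost difference = listed cost difference + h × dH. The listed rule is therefore off by h × dH in absolute size.

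**Case 1: a charged admission that replaces home days one for one.** Here dH = -dNH. The listed rule gives n × dNH, and the full figure is (n - h) × dNH. The overstatement factor is n/(n - h) = 1/(1 - h/n):

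- h/n = 0.3: 1/0.7 = 1.43
- h/n = 0.5: 1/0.5 = 2.0
- h/n = 0.7: 1/0.3 = 3.33

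Per resident, with n = 100 units and 91 nursing-home days per placed resident (half of a 182-day follow-up), all assumed:

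| Placement, control vs intervention | dNH | Listed | Full, h/n 0.3 | 0.5 | 0.7 |
|---|---|---|---|---|---|
| 6% vs 6% | 0 | 0 | 0 | 0 | 0 |
| 6% vs 4% | -0.02 × 91 = -1.82 | -182 | -127 | -91 | -55 |
| 10% vs 5% | -0.05 × 91 = -4.55 | -455 | -319 | -228 | -137 |

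The error is 55 to 127 units for a 2-point placement difference, 137 to 319 for a 5-point difference, and zero when placement is equal.

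**Case 2: survival.** If mortality differs by 2 or 5 points and each death avoided adds 91 home days (assumed), the home-day cost left out is 0.02 × 91 × h = 55, 91 or 127 units per resident, or 0.05 × 91 × h = 137, 228 or 319 units, for h/n = 0.3, 0.5 and 0.7. This does not depend on placement and flatters the arm with better survival.

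**Case 3: placement outside the listed department.** Let c be the share of placement days that the list charges, and assume all nursing-home days cost n. The listed rule gives c × n × dNH against a full (n - h) × dNH. The two agree when c = 1 - h/n, that is 0.7, 0.5 or 0.3 for the three ratios. Above that share the effect of placement on cost is overstated, and below it understated. The documents do not give c.

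**The case against.** A reader might infer that every nursing-home placement is charged gross and that the cost difference is simply wrong. The documents do not support that, for three reasons.

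- **Scope of the charge.** Only admissions to the nursing home's medical department are listed. Placement is a separate outcome, and nothing says that its days are costed. The Background says that about half of residents have dementia, and the article does not say which department they would enter. A temporary admission may also leave the home place occupied, so that no home days are released. Case 3 shows that the direction can reverse.
- **Conditionality.** Stay costs common to both arms cancel. No document shows or predicts a placement or mortality difference of a given size within six months.
- **Ambiguity.** The sentence on resource use registered in the home, and the one on valuing care consumption, leave open that some in-home care is counted.

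It can also be argued that lodging and domestic help lie outside direct healthcare costs, so that leaving them out is a choice of scope. That is fair for those items. It is less persuasive for nursing and personal care, and it does not explain why a nursing-home admission is priced while the home days it replaces are not, under a perspective called societal.

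These points limit the claim. They do not remove it: the article gives an explicit list, the list is asymmetric, and the sentence on home registration names a data source and not a cost category.

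**Conclusion.** The point stands in conditional form. If the list is followed, the cost difference is biased whenever home days or in-home care differ between arms, by h times the difference in home days plus any unpriced change in care. It is unaffected when both are equal. For a charged admission that does replace home days, the overstatement is 1.43, 2.0 or 3.3 times at assumed price ratios of 0.3, 0.5 or 0.7. The prices, placement and mortality differences and the 91 days are all assumptions. The documents establish an asymmetric costing rule; they do not establish a demonstrated error or a fixed direction. It is a modest and inexpensive improvement to the economic analysis.

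**What to change.** In the Economic evaluation section, add to the included cost categories, for both arms: days resident in the home for the elderly, from baseline to placement, death or 6 months, valued at a guideline day price on the same basis as nursing-home days.

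Three conditions go with it:

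- Add in-home nursing or personal care as a separate item only if the day price does not already contain it and the home's registration records it. Otherwise care is counted twice, or cannot be counted.
- State whether placement outside the medical department is charged. If home days stop at placement and the new days carry no price, the placement would appear as a saving.
- Say what the resource use registered within the home covers and whether it enters total costs.

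The days follow from placement and death dates already planned, so the cost is one line in the cost definition and a little more analysis. Whether care use can be added depends on what the registration holds, which the article does not say. The downside is that any apparent saving from avoided admissions, or any apparent value from better survival, becomes less favourable.
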